## Abstract

**Background:**

Recent studies suggest that excessive gestational weight gain (GWG) leads to adverse maternal and fetal outcomes including weight retention in the mother and an increased risk of childhood obesity in the offspring.

The aim of the GeliS study is to examine the effect of a lifestyle intervention programme during pregnancy to avoid excessive GWG and, hence, to reduce pregnancy and obstetric complications as well as the risk of maternal and offspring obesity.

**Methods and design:**

The GeliS study is a multicentre cluster-randomized controlled trial. A total number of 2500 pregnant women (singleton pregnancy) with a pre-pregnancy BMI ≥ 18.5 kg/m^2^ and ≤ 40 kg/m^2^ will be recruited in practices of gynaecologists and midwives in ten Bavarian regions. The intervention comprises three structured and individualised counselling sessions on a healthy diet, regular physical activity as well as weight monitoring during pregnancy and one session after delivery, respectively. The counselling sessions are attached to routine pre- and postnatal visits using standardised materials and procedures. In the control regions, general recommendations for a healthy lifestyle are given. An oral glucose tolerance test is offered to all participants.

The primary outcome is the proportion of participants with excessive GWG. Secondary outcomes include pregnancy and obstetric complications such as frequency of gestational diabetes, preeclampsia and caesarean sections as well as weight retention in the mothers and BMI and other health variables in the offspring. A 5-year follow-up of both mothers and their infants is planned.

**Discussion:**

The GeliS lifestyle intervention programme has been adapted to the existing routine health care system for pregnant women. If shown to be effective, it could be immediately implemented in routine care.

**Trial registration:**

The study protocol is registered at the ClinicalTrials.gov Protocol Registration System (NCT01958307).

## Background

The global prevalence of overweight and obesity has reached an epidemic dimension. In this context, the prevalence of overweight and obesity among women of reproductive age increased substantially [1,2]. Maternal overweight or obesity is associated with a variety of pregnancy and obstetric complications [3-7], such as gestational diabetes mellitus (GDM) [8], preeclampsia [9-11] and an increased risk for macrosomia [12] and caesarean delivery [13,14].

Likewise, recent data suggest that excessive GWG may result in a similar risk profile. Excessive GWG was found to be associated with an increased risk for many adverse maternal and fetal outcomes [15,16] such as large for gestational age (LGA) newborns [17-19] and long-term maternal weight retention after delivery [20-23]. Furthermore, GWG has been reported to be a significant risk factor for childhood obesity [24-33].

To support an optimal pregnancy outcome, the US Institute of Medicine (IOM) provided recommendations for GWG stratified according to BMI of the women before pregnancy [16]. Unfortunately, in many countries including the USA, but also in Germany, an increasing proportion of pregnant women exceed these recommended thresholds [16,25,34,35].

Growing evidence suggests that lifestyle during pregnancy and in the early postnatal period is considerably influencing fetal and infant growth and development. This is an important observation, as pregnancy and the early postnatal period represent critical stages of development for the offspring and may “programme” the risk of metabolic disorders later in life [36,37]. To interfere with this potentially vicious cycle [38,39], adequate intervention strategies which can be introduced into medical practice are urgently required. Some recent studies focussing on a healthy lifestyle during pregnancy and consisting of a balanced diet and regular physical activity showed a reduction in the risk of excessive GWG [40-43].

We recently performed the FeLIPO study (acronym for “Feasibility of a lifestyle intervention in pregnancy to optimize maternal weight development”) to assess the potential to prevent excessive GWG by a simple lifestyle intervention [44]. The 2-session intervention programme focussing on a healthy diet, regular physical activity, and self-monitoring of body weight resulted in a significantly lower proportion of women exceeding the IOM recommendations among women in the intervention group (38%) compared to the control group (60%, p < 0.05) [44]. Similar to the results of a recent meta-analysis [45], the FeLIPO study detected a trend for a decreased risk of developing gestational diabetes in the intervention group [44].

Based on the results of this pilot study we are planning to examine the potential of a comprehensive lifestyle programme in pregnant women under “real life” conditions. The GeliS project (acronym for “Gesund leben in der Schwangerschaft”/healthy living in pregnancy) is a public health approach focussing on the prevention of excessive GWG by lifestyle counselling on diet and physical activity during pregnancy, and by self-monitoring GWG using weight gain charts. The lifestyle intervention programme has been adapted to the German health care system to allow immediate implementation if it is shown to be effective at reducing the rate of excessive GWG and associated risks.

## Methods and design

### Study design and setting

The GeliS trial is a multicentre and multidisciplinary public health project in ten regions of Bavaria, a federal state of Germany, targeting maternal and fetal health. It is designed as a prospective, cluster-randomized, controlled, open intervention trial. We perform a paired cluster-randomization by matching five pairs of regions according to birth figures, sociodemographic and geographic criteria. Randomization is performed within these pairs and each pair is supervised by an expert centre for nutrition run by the Bavarian State Ministry of Food, Agriculture and Forestry.

Adherence to the study protocol is monitored by the Münchner Studienzentrum at the Technical University of Munich. The Münchner Studienzentrum is furthermore in charge of comprehensive data management according to current standards. The study will be conducted in accordance with the declaration of Helsinki as well as with current local regulatory requirements and laws. Written informed consent will be given by all participants. The study protocol was approved by the ethical committee of the Technical University of Munich and registered at the ClinicalTrials.gov Protocol Registration System (NCT01958307).

### Power calculation

The sample size was calculated based on the proportion of women exceeding weight gain recommendations according to the Institute of Medicine (IOM) guidelines and the results of the FeLIPO study which was conducted as a pilot study [44]. In accordance with data from the Bavarian perinatal register, it is expected that at least 40% of the women (BMI > 18.5 kg/m^2^) will exceed the threshold levels of IOM in the control group ([name], November 2009, personal communication on the basis of Bavarian perinatal data from 2007). A decrease to 30% in the intervention group by adopting the lifestyle intervention programme is assumed. To detect this difference in proportions with 90% power using a significance level (alpha) of 0.05 and an intraclass correlation coefficient of 0.5% [46], 1900 pregnant women are needed [47]. To compensate for a possible imbalance in the sample sizes between groups as well as a drop-out rate of up to 25% until delivery, 2500 participants are required for the trial and it is planned to recruit these women in both urban and rural regions reflecting the socioeconomic conditions in the Bavarian population.

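### The stated 90% power makes no allowance for estimating between-region variance from five regions per arm; on the plan's own inputs an unadjusted region-level t test has about 82%

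*Protocol article*

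**What the plan says.** The Power calculation section of the protocol article gives these inputs for the primary outcome, the proportion of women with excessive gestational weight gain:

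- Control rate: "it is expected that at least 40% of the women" exceed the recommended gain.
- Intervention rate: "A decrease to 30% in the intervention group by adopting the lifestyle intervention programme is assumed".
- Error rates: "To detect this difference in proportions with 90% power using a significance level (alpha) of 0.05".
- Clustering and size: "an intraclass correlation coefficient of 0.5% [46], 1900 pregnant women are needed [47".
- Inflation for imbalance between groups and losses: "a drop-out rate of up to 25% until delivery, 2500 participants are required for the trial".

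The section Study design and setting fixes the unit of randomisation: "We perform a paired cluster-randomization by matching five pairs of regions", with allocation made within each pair. There are therefore five regions per arm. The power paragraph gives no number of clusters, cluster size, matching gain or small-sample allowance, and it does not say whether alpha is one- or two-sided. The article names no primary test.

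**The concern.** A design effect corrects the variance of the treatment comparison for clustering. If normal critical values are then used, the between-region variance is treated as known. Here it must be estimated from ten regions. That leaves 8 degrees of freedom if the matching is ignored and 4 if the pairs are kept. The two-sided 5% critical values become 2.31 and 2.78 instead of 1.96, and power falls accordingly.

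The statement concerns the primary outcome, and the Discussion ties a favourable result to roll-out in routine care. If the real type II error is nearer 18% than 10%, a null result would be read with more confidence than the design supports.

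**Working it through.** **Inputs.** From Power calculation: p1 = 0.40, p2 = 0.30, alpha = 0.05, power 90%, ICC = 0.005, N = 1900. From Study design and setting: 5 regions per arm in 5 pairs. Assumed: two-sided alpha and equal region sizes, so m = 1900/10 = 190.

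**Step 1: reproduce 1900.**

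- Unpooled normal theory: n per arm = (1.960 + 1.282)² × (0.24 + 0.21) / 0.10² = 10.507 × 0.45 / 0.01 = 473.
- Pooled variance under the null: [1.960 × √(2 × 0.35 × 0.65) + 1.282 × √0.45]² / 0.01 = 476.01, rounded up to 477. With continuity correction: 496.
- Design effect: 1 + (190 − 1) × 0.005 = 1.945.
- Totals, 2 × n × 1.945: 1839, 1856 and 1929.

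These bracket 1900 and lie within about 3% of it. One-sided alpha gives only 1509 to 1587, so two-sided is the reading that fits. Clusters of 10 to 50 women would give totals of only about 1000 to 1190, so the size used appears to be that of a region.

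**Step 2: normal-theory power at 1900.**

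- SE = √[(0.24 + 0.21) × 1.945 / 950] = 0.03035.
- Noncentrality = 0.10 / 0.03035 = 3.29.
- Power = Φ(3.29 − 1.96) = 90.9% (90.7% with the pooled formula). This agrees with the stated 90%.

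**Step 3: same inputs, t reference.** Power is taken from the noncentral t distribution with noncentrality 3.29.

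| Evaluable women | Normal | 8 df (matching ignored) | 4 df (paired, no matching gain) |
|---|---|---|---|
| 1900 | 90.9% | 82.2% | 69.6% |
| 1875 (2500 less 25%) | 90.7% | 81.9% | 69.3% |
| 2500 (no losses) | 94.0% | 86.7% | 74.9% |

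A beta-binomial simulation of 100,000 trials at 190 women per region gives 82.3% (8 df) and 69.7% (4 df).

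**Step 4: what matching would have to deliver.** Let f be the share of between-region variance left after matching. Then SE = √{0.45 × [(1 − 0.005)/190 + f × 0.005] / 5}, and power is taken on 4 df.

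| Share removed (1 − f) | Paired power |
|---|---|
| 0% | 69.6% |
| 25% | 74.9% |
| 50% | 80.6% |
| 75% | 86.5% |
| 90% | 90.1% |
| 100% | 92.3% |

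**Step 5: could 1.96 be kept?** With an estimated region-level standard error, the two-sided tail area beyond 1.96 is 8.6% on 8 df and 12.2% on 4 df. Simulation under the null gives 8.5% and 12.1%. Both exceed the stated 0.05.

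**Step 6: detectable difference and ICC range.** At 90% power the detectable difference on 8 df is about 11.3 points with the SE held at its planning value. It is 11.2 points if the intervention-arm variance is recomputed. For a 10-point difference at 190 women per region:

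| ICC | 8 df | 4 df, no matching gain |
|---|---|---|
| 0.0025 | 91.1% | 80.5% |
| 0.005 (plan) | 82.2% | 69.6% |
| 0.01 | 66.0% | 53.6% |

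**The case against.** The best defence has five parts.

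- **The regions were not overlooked.** This stands. About 190 women per region is what brings the calculation close to 1900. A reader might infer that the plan ignored having only ten regions; the figures do not support that. Only the degrees of freedom are missed. The reconstruction is also an inference, since the cited sample size method is not visible and no variant gives exactly 1900.
- **Some valid tests could reach 90%.** This stands too. It would be too strong to say that no test holding alpha at 5% has 90% power. The paired test gets there if matching removes about 90% of the between-region variance, and the 8-df test gets there if the effective ICC is about 0.0025, for example after covariate adjustment. The article claims neither.
- **70% is a worst case.** Agreed. Matching on birth figures, sociodemographic and geographic criteria is meant to bring a gain, so 70% should not be quoted without its condition.
- **The analysis may be handled properly in an analysis plan that is not shown.** This is why the point rests on the power statement alone. A reader might infer that the trial will be analysed with an anti-conservative z or sandwich test, or be held to the smallest two-sided p of 2/32 = 0.0625 that an exact test on five pairs allows. The article adopts neither method, so no such conclusion follows. The type I error figures show only that the 90% cannot be rescued by keeping 1.96.
- **2500 women are recruited.** The extra women cover imbalance and losses of up to 25%, which leaves 1875. Even with no losses, the 8-df test has 86.7%.

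**Conclusion.** The concern holds as a criticism of the stated power. The normal-theory arithmetic is sound and gives about 91%. It makes no allowance for estimating between-region variance from five regions per arm. On the plan's own inputs the unadjusted region-level test has about 82% power on 8 df, so the type II error is about 18% instead of 10%. The paired test has about 70% with no matching gain and about 81% if matching removes half the between-region variance.

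These figures assume two-sided alpha, an ICC of exactly 0.005 and equal region sizes; unequal sizes would lower power further. The results at ICC 0.0025 and 0.01 are a sensitivity range and not evidence that the plan's ICC is wrong. Nothing here shows that the sample size is unusable or that the eventual analysis is invalid.

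**What to change.** Keep 1900 evaluable and 2500 recruited women, and revise the power paragraph as follows:

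1. State that 1900 women in ten regions give about 82% power for 40% v 30% on 8 df, or 90% power for a difference of about 11.3 points.
2. Give the paired figure on 4 df together with the matching gain assumed: about 70% with none, about 81% with half of the between-region variance removed.
3. State that the figure presumes a primary test with small-sample degrees of freedom for ten regions, and that alpha is two-sided if that is meant.
4. Show power for ICC 0.0025 to 0.01 (8 df: about 91% to 66%).

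The cost is a few sentences and a less favourable stated power; no extra women are needed. If 90% for a 10-point difference is to be kept without a matching gain, more regions would be needed: six per arm at 190 women each on the unpaired test (90.1%, or 12 × 190 = 2280 evaluable women), or seven to eight pairs on the paired test (89.8% and 94.4%). That is a design change, and the restatement does not depend on it.

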#### Drop-out criteria

Reasons for drop-out are complications during pregnancy as assessed by the trial physician. Women who give birth preterm (delivery before 37^th^ week of gestation) will be excluded from the GWG analysis. These and other reasons for drop-out are carefully documented.

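### At the stated 25% drop-out ceiling, 2500 recruits leave 1875 women, not the 1900 required, so the target holds no allowance for group imbalance; the effect on power is small

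*Protocol article*

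**What the plan says.** The Power calculation section assumes an excessive-gain rate of at least 40% in the control group and 30% in the intervention group. With 90% power, alpha 0.05 and an intraclass correlation of 0.5%, it arrives at 1900 women. It then gives the reason for recruiting more: "To compensate for a possible imbalance in the sample sizes between groups" and, in the same sentence, "as well as a drop-out rate of up to 25% until delivery, 2500 participants are required for the trial". The size of the imbalance is not given, and the extra 600 women are not divided between the two purposes.

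Two other places bear on the point. Study design and setting gives the clusters: "We perform a paired cluster-randomization by matching five pairs of regions", so ten regions, five per arm. Drop-out criteria says: "Women who give birth preterm (delivery before 37^th^ week of gestation) will be excluded from the GWG analysis". That sentence stands among the reasons for drop-out, and the next one refers back to these and other such reasons.

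**The concern.** The sentence names two allowances and gives one number. If drop-out at the stated ceiling already uses the whole margin, the second allowance exists only in words.

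Imbalance is a realistic prospect here. Whole regions are randomised, and the number of women per arm depends on which practices join and how many women they enrol. The authors saw this risk and stated that it was covered. Anyone following recruitment would take 2500 as a target that still holds some reserve at 25% loss. What is at stake is the accuracy of a stated sample-size figure and of the reserve it is said to contain.

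**Working it through.** **Inputs.** From Power calculation: 40% versus 30%, 90% power, alpha 0.05 (sidedness not stated; two-sided assumed), intraclass correlation 0.005, 1900 needed, drop-out up to 25%, 2500 recruited. From Study design and setting: ten regions, five per arm. The article cites a method for the 1900 but prints no formula, so a normal approximation is used below.

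**1. Reproducing the 1900.** With 1900/10 = 190 women per region, the design effect is 1 + 189 × 0.005 = 1.945.
- Two-proportion formula with pooled variance: 477 per arm; 477 × 1.945 × 2 = 1856, 2.3% below 1900.
- Same formula with continuity correction: 496 per arm; 496 × 1.945 × 2 = 1929, 1.5% above 1900.

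The 1900 lies between the two and is accepted as the plan's requirement.

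**2. Inflating for drop-out alone.**
- Needed: 1900/(1 − 0.25) = 2533.3, so 2534.
- Delivered: 2500 × 0.75 = 1875, which is 25 short; 25/1900 = 1.3%.
- Break-even drop-out: 1 − 1900/2500 = 24.0%.

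**3. Adding imbalance.** No arm ratio is stated, so two are assumed. The simple inflation factor for a ratio r:1 is (1 + r)²/(4r).

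| Ratio | Factor | Evaluable needed | Recruits at 25% loss | Drop-out that 2500 tolerates |
|---|---|---|---|---|
| 1:1 | 1.0000 | 1900 | 2534 | 24.0% |
| 1.25:1 | 1.0125 | 1924 | 2565 | 23% |
| 1.5:1 | 1.0417 | 1979 | 2639 | 21% |

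The last column is 1 − (evaluable needed)/2500. The factor ignores clustering. With a fixed number of regions per arm, the between-region part of the variance does not grow when women are split unequally, so the factor somewhat overstates the cost of imbalance.

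**4. Power at 1875, equal arms.** There are 187.5 women per region. The design effect is 1 + 186.5 × 0.005 = 1.9325, and the effective number per arm is 937.5/1.9325 = 485.1.
- Unpooled variance: standard error √(0.45/485.1) = 0.03046; 0.1/0.03046 − 1.96 = 1.323; power 90.7%.
- Pooled variance under the null: null standard error √(0.455/485.1) = 0.03063; (0.1 − 1.96 × 0.03063)/0.03046 = 1.312; power 90.5%.

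The same steps at 1900 give 90.9% and 90.7%. The missing 25 women cost about 0.2 percentage points.

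**5. Power at 1875, 3:2 arms.** The arms are 1125 and 750, or 225 and 150 per region. The design effects are 1 + 224 × 0.005 = 2.12 and 1 + 149 × 0.005 = 1.745, giving effective numbers of 530.7 and 429.8. Power is 89.9 to 90.3%, depending on the variance form and on which arm is larger.

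**The case against.** There are four serious points on the other side.

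- **Rounding.** Taking 2534 down to 2500 is a 1.3% difference that few would query. This accounts for the 25 women. It does not account for the claim that the same 2500 also covers imbalance, because rounding down removes margin.
- **The 25% is a ceiling.** At 20% loss, 2000 women remain, which is 100 above 1900 and enough even for 1.5:1 by the simple factor (1979). This stands as far as it goes: below 24% there is some reserve. But the plan offers the two allowances together at up to 25%, and there the reserve is gone.
- **Power hardly moves.** A reader might infer that the trial is underpowered. The figures do not support that. By the pooled formula 90% power needs 477 effective women per arm, and 1875 supplies 485.1. If the 1900 came from a continuity-corrected formula (496 per arm), that margin disappears, but 1900 itself, with 950/1.945 = 488.4, would also fall short. The gap between 1875 and 1900 stays small either way.
- **Preterm births.** A reader might infer that the preterm exclusion comes on top of the 25% and makes the shortfall much larger. The natural reading is the opposite. The exclusion is listed under Drop-out criteria, the next sentence treats the items there as reasons for drop-out, and preterm delivery occurs by the end of the period to which the 25% applies. The protocol gives no preterm rate from which an extra loss could be computed.

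**Conclusion.** The sentence is wrong as written, and the correction is minor. At the drop-out the plan says it covers, 2500 gives 1875 evaluable women and contains nothing for imbalance. This uses only the plan's own figures and needs no assumption about the formula behind 1900.

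The finding is a claimed reserve that is absent at the ceiling. It is not a finding of inadequate power. Power stays at about 90.5 to 90.7% with equal arms and about 90% at 3:2. Those power figures rest on a two-sided 5% test, a normal approximation, an intraclass correlation of 0.005 and five equal-sized regions per arm. The effects of having few regions and of unequal region sizes are separate questions. They are not caused by the 25 women and play no part in this conclusion.

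**What to change.** Reword the last sentence of Power calculation:

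- State that 2500 recruits give 1875 evaluable women at 25% total loss, with preterm exclusions counted within that loss in line with Drop-out criteria.
- Quote the power at 1875, with the formula used.
- Either remove the claim that 2500 also compensates for imbalance, or give the drop-out it tolerates at a named arm ratio: 24.0% with equal arms, about 23% at 1.25:1, about 21% at 1.5:1 by the simple factor.

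This needs no extra recruitment and no change to design or analysis. The only downside is that the stated reserve looks slightly less favourable.

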### Study population

#### Inclusion criteria

Women aged 18 to 43 years with a singleton pregnancy, a pre-pregnancy BMI ≥ 18.5 kg/m^2^ and ≤ 40 kg/m^2^, and sufficient German language skills are eligible for the study. These pregnant women are recruited before the 12^th^ week of gestation and written informed consent is mandatory.

#### Exclusion criteria

Exclusion criteria are multiple pregnancy, high risk pregnancy prohibiting study participation (contraindications to exercise e.g. placenta praevia, persistent bleeding, cervical incompetence etc.), pre-pregnancy diabetes mellitus or early gestational diabetes, uncontrolled chronic diseases (e.g. thyroid dysfunction), psychiatric or psychosomatic diseases, and any other diseases which could interfere with compliance according to the study protocol.

